#### Sample size calculation

Since there is no clinical trial assessing the effect of intestinal flora on the bioavailability of chemotherapy drugs and the intervention endpoints of intestinal flora are currently unable to determine, the sample size is estimated based on the data from a previous clinical trial [22] which assessed the effects of synbiotics intervention on chemotherapy-related adverse effects (including diarrhea, appetite loss, nausea, and vomiting) for CRC patients received post-operative chemotherapy, showing that 20 volunteers per group had 90% power at an alpha level of 0.05 to detect significant differences. Combined with the above data from the clinical trial, the sample size in this study will be calculated statistically by the Power Analysis and Sample Size Software (PASS). Considering the long duration of the study (3 months) and the expected withdrawal of participants during the intervention, we plan to recruit *n* = 25 participants per group (*n* = 100 total).

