#### Data collection and sample handling

The overall study design is depicted in Fig. 1. Assessment of participants will be conducted at the perioperative (baseline = week 0), pre-treatment (week 3), post-treatment (week 15), and in each chemotherapy cycle. The primary outcomes will be the differences in the microbiota composition at different CRC tumor sites and differences in gut microbiota composition, adverse reactions, and blood concentration of capecitabine in patients with CRC treated for 12 weeks with XOS or placebo. The secondary outcomes will include blood indicators (hepatic and renal function, blood glucose, blood lipid, and inflammatory cytokines), SCFAs concentration, QoL, and mental health.

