#### Adverse effects

Adverse effects, including nausea, vomiting, diarrhea, leukopenia, anemia, thrombocytopenia, diarrhea, oral mucosal reaction, peripheral neuropathy, hand-foot syndrome, pigmentation, and abnormal liver function, will be assessed in each chemotherapy cycle using the Common Terminology Criteria for Adverse Events (CTCAE) version 5.0 [40]. Patients will be informed of the types of all adverse effects prior to the start of the experiment. After the beginning of the experiment and before each chemotherapy treatment, all adverse effects will be questioned and recorded from grades I to IV according to severity in the office. There is no knowledge of the possibility of any discomfort or adverse event with this supplementation. Participants are asked to inform the investigators in time if there is any adverse event that may be associated with prebiotics. These adverse events will be recorded by investigators. Protocol modifications will be communicated to the ethics committee through an official modification request, and the participants will be notified by telephone.

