#### Data analysis

The visiting time of the participants is in accordance with the treatment course, so as to facilitate the retention of the participants. The measured data for each visit will be collected on paper and then recorded electronically on a secure, locked office computer. The paper version of the data will be locked in a bookcase. Only the investigators running in the study will have access to the final study dataset.

The obtained data will be analyzed by the SPSS software V26.0 (IBM, USA). Continuous data will be expressed as mean ± standard deviation (SD), and categorical data will be expressed as the number of cases (*n*) and percentage (%). Differences in parameter continuous variables and asymmetric variables between groups will be analyzed through independent samples *t* test and Mann-Whitney *U* test, respectively, using a paired *t* test to assess the effect of the intervention in each group. The normality of data will be assessed using the Kolmogorov-Smirnov test.

The results will be regarded as statistically significant if *p* values< 0.05.

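### Four unranked primary outcomes are each open to a claim at p < 0.05, and the only power figure concerns adverse effects

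*Protocol article*

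**What the plan says.** The section Data collection and sample handling sets the primary outcomes in one sentence. Its first part reads "The primary outcomes will be the differences in the microbiota composition at different CRC tumor sites". This compares left-sided with right-sided tumours and is not randomised. The second part adds "differences in gut microbiota composition, adverse reactions, and blood concentration of capecitabine in patients with CRC treated for 12 weeks with XOS or placebo", which makes three randomised comparisons. The Abstract gives the same four. Neither place ranks them or says whether one success is enough.

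Data analysis closes with "The results will be regarded as statistically significant if" p falls below 0.05. It makes no distinction between primary and other results.

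Sample size calculation takes its figure from a previous synbiotic trial of chemotherapy-related adverse effects ("including diarrhea, appetite loss, nausea, and vomiting"), "showing that 20 volunteers per group had 90% power at an alpha level of 0.05 to detect significant differences". The same section says that no earlier trial addresses drug bioavailability and that endpoints for the flora could not be determined. Recruitment is 25 in each of four groups, 100 in all. The article does not say whether XOS and placebo are compared within each tumour location or across both.

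**The concern.** With four routes to a primary claim and a full 0.05 on each, the chance of at least one false claim exceeds 5%. A chance difference in capecitabine level, or in one feature of the gut flora, could be reported as a positive primary result for XOS with nothing in the article to qualify it.

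The power statement does not help the reader weigh such a result. It belongs to one of the four outcomes, and that outcome is not reduced to a single comparison. For the other three, neither a positive nor a null result can be set against a planned power.

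**Working it through.** **Inputs.** Four primary outcomes, three of them randomised (Data collection and sample handling). Threshold 0.05 (Data analysis). 90% power, alpha 0.05, 20 per group (Sample size calculation). Effect size, event rates and sidedness are not given.

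**1. The plan's own figure.** The step from 20 to 25 per group is consistent with 20% withdrawal, 20 / (1 − 0.20) = 25, although no rate is stated. The 90% cannot be reproduced without an effect size. It can only be solved backwards, assuming a two-sided test:

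- Normal approximation: d = (1.960 + 1.282) × √(2/20) = 1.025.
- t test: d = 1.052.
- For a binary event, 90% power would need rates such as 50% v 6%, 60% v 13% or 70% v 21%.

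None of these values is in the article. They serve below as assumptions only.

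**2. Chance of at least one false primary claim, no true differences.** For k independent tests at 0.05 it is 1 − 0.95^k.

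- All four primaries: 1 − 0.95⁴ = 0.185.
- The three XOS v placebo primaries: 1 − 0.95³ = 0.143.

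For four two-sided normal tests with equal pairwise correlation, simulation (50,000 draws) gives:

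| Correlation | Chance of at least one false claim |
|---|---|
| 0.3 | 17% |
| 0.5 | 16% |
| 0.8 | 11% |

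**3. If an outcome is itself several tests.** The Adverse effects section has 12 entries, 11 of them distinct because diarrhea appears twice. Eleven tests at 0.05 give 1 − 0.95¹¹ = 0.431 if independent, about 30% at correlation 0.5 and 18% at 0.8. This shows the direction only; the article does not say that each term is tested.

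**4. Power if alpha is split over four.** The Bonferroni level is 0.05 / 4 = 0.0125, with critical value 2.498. Using d from step 1 and the normal approximation:

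- 20 v 20 within one location: Φ(1.025 × √(20/2) − 2.498) = Φ(0.744) = 77%; the t test gives 76%.
- 40 v 40 with locations pooled: Φ(1.025 × √(40/2) − 2.498) = Φ(2.087) = 98%; the t test also gives 98%.

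Within one location, 28 evaluable patients per group would restore 90%. With no split, power for each comparison is unchanged.

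**The case against.** **An analysis plan may deal with this.** A journal article need not set out a multiplicity procedure, and its absence alone would be no finding. Here, though, the article states the decision rule and lists four outcomes of equal rank, and its sample size uses the same 0.05. A plan that ranked or adjusted them would change what is published.

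**The tumour-site comparison cannot yield a claim about XOS.** This stands. For a claim about the intervention, the relevant figure is 14.3% rather than 18.5%.

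**The outcomes are likely to be correlated.** This also stands, and it makes the independent-test figures upper values for three or four tests. The excess over 5% remains.

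Several stronger readings are tempting, but the text does not support them:

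- *Forty-four adverse-effect tests.* Eleven terms over four cycles (12 weeks in 3-week cycles) would give 1 − 0.95⁴⁴ = 89.5% under independence. But the article only schedules assessment in each cycle. It does not plan a test of each term in each cycle, and independence is implausible within the same patients: the figure is about 59% at correlation 0.5 and 29% at 0.8.
- *The 90% power fails.* Under the unadjusted rule, power per comparison is untouched. It changes only if alpha is split, or if all four outcomes must succeed. For the other three outcomes power is unknown, which is not the same as inadequate.
- *The 90% belongs to one adverse-effect comparison.* The article ties it to a set of effects and identifies no comparison.
- *No test fits graded adverse effects.* Data analysis names the Mann-Whitney test, which can handle ordinal grades.
- *Appetite loss was dropped from the endpoint.* Its mention in the sample-size section describes what the earlier trial assessed, so its absence from this trial's list is no contradiction.

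**Conclusion.** The point holds in limited form. The published rule allows any of four unranked primary outcomes to be claimed at 0.05. Taking one test per outcome and no true differences, the chance of at least one false primary claim is 18.5% for all four and 14.3% for the three randomised comparisons if independent. For four it is about 11% to 16% at correlations of 0.8 to 0.5. More than one test per outcome would raise these figures.

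The 90% power figure cannot be reproduced from the article and covers adverse effects only. What power would be after an alpha split depends on an effect size that the article does not give and on whether locations are pooled, so no single reduced figure should be put in its place.

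**What to change.** In Data collection and sample handling and in Data analysis:

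1. Make one patient-level adverse-effect summary the first primary test of XOS against placebo, stratified by tumour location.
2. Test capecitabine level, then one named gut-microbiota measure, in that fixed order at 0.05, each only if the test before it succeeds. Holm's procedure across the three is an alternative.
3. Report tumour-site microbiota as a separate, non-randomised aim.
4. Report individual adverse-effect terms and cycles descriptively.

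In Sample size calculation, say that the 90% applies to adverse effects only, and give the comparison and effect size behind it.

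If all four stay primary at 0.0125 each, restate power for the analysis actually used. Under the back-solved effect size (d about 1.03 to 1.05) that is about 76% to 77% for 20 v 20 within a location, or about 98% for 40 v 40 pooled. The two must not be mixed.

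The change should be dated and made before the allocation is unblinded for analysis. It needs no new data or patients. The price is that some outcomes lose stand-alone primary status, or that the stated power changes.

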## Discussion

CRC is one of the most prevalent cancers worldwide. Postoperative adjuvant chemotherapy for CRC is a helpful attempt in recent years. However, the adverse effects during chemotherapy and the inter-individual variation in drug efficacy are still relatively big problems. Moreover, the different primary tumor locations may result in differences in intestinal flora composition and prognosis. Efforts to find a kind of safe food with therapeutic effect and to evaluate its impact on patients with CRC at different primary tumor locations are critical. Studies have revealed the vital part of intestinal flora in the progression and treatment of CRC [5, 12, 46], and the concept of “pharmacomicrobiomics” is increasingly recognized [47]. Targeting intestinal flora, therefore, may modulate the efficacy and adverse effect of chemotherapy.

Both animal and human studies provide strong evidence that microecologics play essential roles in preventing chemotherapy-induced mucositis [48]. Bowen et.al. [49] have revealed the effects of VSL#3, a mixture of *Lactobacilli*,* bifidobacteria*, and* streptococcus*, on preventing diarrhea following chemotherapy with irinotecan in rats. Synbiotics have significantly reduced the occurrence of severe lymphopenia and diarrhea and increased levels of *Bifidobacterium* and *Lactobacillus* species and concentrations of SCFAs in esophageal cancer patients undergoing neoadjuvant chemotherapy [50]. Dietary supplementation of prebiotics (oligofructose and inulin) can enhance the efficacy of six cytotoxic drugs and prolong the lifespan of rodents with transplantable malignant tumors [51, 52]. XOS is a mixture of oligosaccharides which can be considered as a prebiotic [53]. XOS can modulate the diversity of intestinal flora, effectively multiply favorable bacteria such as bifidobacteria, and produce beneficial metabolites including SCFAs [54]. In addition, it has been reported that XOS are beneficial to type 2 diabetes mellitus [55], diarrhea [33], and constipation [32]. However, so far, there is no study evaluating the role of XOS consumption on the intestinal flora in patients with CRC.

This study will reveal the potential benefits of prebiotic for improving the gut microbiota composition, alleviating the adverse effects, and improving the efficacy of chemotherapy in patients with CRC. In addition, our study will provide data on the different distribution of tumor microbiota and the different changes of gut microbiota during treatment in LSCRC and RSCC, which may provide novel insights into personalized cancer treatment strategies based on primary tumor locations and gut microbiota in the future. 

## Trial status

This trial was registered at ClinicalTrials.gov, and this article is based on the 2nd version of the protocol published in September 2021. It was not submitted earlier to be published due to changes in the study status. The recruitments have begun beginning of June 2021, and due to the COVID-19 pandemic, the patient inclusions were delayed to resume by October 2022. The final inclusion will be terminated 1 March 2023.

## Protocol amendments

A second version of this protocol was conveyed in regard to the post-treatment visit (visit 2).

## Data Availability

Not applicable.

## Abbreviations

CRC: Colorectal cancer
SCFAs: Short-chain fatty acids
LSCRC: Left-sided colorectal cancer
RSCC: Right-sided colon cancer
QoL: Quality of life
XOS: Xylooligosaccharide
SPIRIT: Standard Protocol Items: Recommendations for Interventional Trials
ULN: Upper limit of normal
PCR: Polymerase chain reaction
OTUs: Operational taxonomic units
PCoA: Principal coordinate analysis
LDA: Linear discriminant analysis
GC-MS: Gas chromatography-mass spectrometry
ELISA: Enzyme-linked immunosorbent assay
TNF-α: Tumor necrosis factor-α
IL-1β: Interleukin-1β
IFN-γ: Interferon gamma
CD3+: T lymphocytes
CD3+CD4+: Helper inducer T cells
CD3+CD8+: Suppressor/cytotoxic T cells
EDTA: Ethylene diamine tetraacetic acid
CTCAE: Common Terminology Criteria for Adverse Events
QLQ-C30: QoL questionnaire-caner 30
HADS: Hospital Anxiety and Depression Scale
